## Methods and analysis

### Study design

The study is a randomized controlled trial with a 3-month intervention and 3-month follow-up period assessing the impact of combined vitamin D and exercise intervention on improving glucose and lipid metabolism in T2DM patients in Xi’an, China (34° N latitude). Vitamin D or placebo supplementation is designed as a double-blind trial. Sixty T2DM patients aged 40–65 years with serum 25(OH)D concentrations < 20 ng/mL on screening will be enrolled during winter and spring through posters and WeChat. Patients will be randomly assigned to either an intervention or a control group. The complete process is outlined in Fig. 1.

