### Setting and participants

#### Inclusion and exclusion criteria

T2DM patients are eligible for study participation if they meet the following inclusion criteria: (a) patients newly diagnosed with T2DM ≤ 1 year, (b) patients with HbA1c level remaining stable at ≤ 8.0% in the past 3 months and patients with no plan of replacing the hypoglycemic agent in the near future, (c) patients without regular vitamin D and/or calcium supplements in the past year, (d) patients who do not meet the current National Physical Activity guidelines [25] in the past year, and (e) with stable body weight (≤ 2 kg variation in weight within the last 3 months.

The following participants were excluded: participants with acute infection; participants experiencing stress; participants experiencing the acute complications of diabetes; participants with heart, liver, and kidney insufficiency, osteoporosis and fracture, and metal implants in the body that could affect magnetic resonance imaging and dual-energy X-ray absorptiometry (DXA) measurements; and participants who have used insulin therapy and have history of sunbathing in the last 6 months.

The criteria for early termination of intervention are as follows: (a) blood calcium level is abnormally high (> 2.65 nmol/L), (b) serum 25(OH)D levels are abnormally high (> 100 ng/mL), and (c) have plan to replace with stronger blood glucose lowering drugs or HbA1c levels are > 8.5%.

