#### Exercise intervention

Patients in the EG or VEG group will perform a 1-h progressively increasing aerobic exercise (cycling, running, or rowing) at 60–80% of maximal heart rate 3 times a week for 3 months [25], and this will be supervised by a qualified trainer who is knowledgeable of the study protocol and procedures. Polar monitor will be used to monitor heart rate during exercise, and the compliance (exercise time and intensity) with each protocol will be recorded. Participants will warm up during the first 5 min on a treadmill at 50–60% of maximal heart rate and subsequently follow the exercise protocol assigned to them, with a 5–10-min recovery exercise at 40–50% of maximal heart rate, which comprises walking and stretching exercise.

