### Data collection

#### Outcome measures and measurement procedures

A full list of measurable outcomes is presented in Table 1. Participants will be assessed at baseline, at the end of intervention, and 3 months after the intervention (Table 2).

**Table 1 Tab1:** Summary of outcome measures

Outcomes	Item	Device

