**Secondary outcomes**		
Body composition	Percent body fat, muscle mass	DXA
	Waist circumference	Standard tape
Metabolic indices	Fasting glucose (G_0_), fasting insulin (I_0_), HbA1c, triglyceride, cholesterol, low-density lipoprotein, and high-density lipoprotein	Fasting blood measurements
Ankle-brachial index	Blood pressure, ABI, baPWV	Validated automatic device
Physical fitness factors	Peak oxygen uptake, maximal heart rate	Cycle ergometer
	Hand grip strength	Hand grip dynamometer

*HOMA* Homeostatic model assessment, *IR* Insulin resistance, *25(OH)D* 25-hydroxyvitamin D, *1,25(OH)*_*2*_*D* 1,25-Dihydroxyvitamin D, *OGTT* Oral glucose tolerance test, *DXA* Dual-energy X-ray absorptiometry, *HbA1c* Glycated hemoglobin, *ABI* Ankle-brachial index

**Table 2 Tab2:** Example template of recommended content for the schedule of enrolment, interventions, and assessments

	Study period				
Timepoint	Enrolment and baseline allocation 0 week	Intervention 1–12 weeks	Post-intervention 13 weeks	Follow-up 13–24 weeks	Close-out 25 weeks

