**Assessment**					
Blood parameter tests	X		X	X	
Body composition	X		X	X	
Ankle-brachial index	X		X	X	
Physical fitness factors	X		X	X	

Analysis of blood samples is as follows: a standard 75-g oral glucose tolerance test (OGTT) will be performed between 0830 and 1100 after a 12-h overnight fast, and venous blood samples will be collected in Venoject-II AutoSep tubes at time points 0, 30, 60, 90, and 120 min to determine the plasma glucose and serum insulin levels. Fasting serum sample will be used to measure the levels of 25(OH)D, 1,25(OH)_2_D, calcium, fasting glucose (*G*_0_), fasting insulin (*I*_0_), HbA1c, triglyceride, cholesterol, low-density lipoprotein, and high-density lipoprotein.

Primary outcomes are as follows: changes in insulin sensitivity and secretion.

Fasting blood glucose and insulin will be used to calculate the insulin resistance index (Homeostatic Model Assessment of Insulin Resistance [HOMA-IR]) and β cell secretion index as follows: HOMA-IR = *G*_0_ × *I*_0_/22.5 and HOMA-β = 20 × *I*_0_/(*G*_0_ – 3.5).

Insulin sensitivity estimated using the Matsuda index of insulin sensitivity during the OGTT will be calculated as follows: 1000/square root of ([*G*_0_ × *I*_0_]) × (mean OGTT glucose concentration × mean OGTT insulin concentration) [27]. Early phase of insulin secretion will be estimated using the insulinogenic index as follows: *I*_30_–*I*_0_/*G*_30_ – *G*_0_ (△I30/△G30), where *I*_30_ and *G*_30_ represent insulin and glucose values at 30 min during the OGTT, respectively [28]. The increments in the area under the curves during the complete 120-min period of the OGTT will be calculated using the trapezoid rule to assess the total changes in glucose and insulin levels [22].

Secondary outcomes are as follows: changes in anthropometry, metabolic indices, ankle-brachial index, and physical fitness factors

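### No blood test is scheduled in weeks 1–12 to trigger the calcium, 25(OH)D and HbA1c stopping criteria; the calcium limit has the wrong unit and the end visit has two times

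*Protocol article*

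**What the plan says.** The section on inclusion and exclusion criteria closes with three lettered reasons for stopping the intervention early:

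- (a) "blood calcium level is abnormally high (> 2.65 nmol/L");
- (b) "serum 25(OH)D levels are abnormally high (> 100 ng/mL");
- (c) patients "have plan to replace with stronger blood glucose lowering drugs or HbA1c levels are > 8.5"%.

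The outcome-measures section takes calcium, 25(OH)D and HbA1c from the fasting study sample. It sets the times as follows: "Participants will be assessed at baseline, at the end of intervention, and 3 months after the intervention (Table 2"). In Table 2 the row "Blood parameter tests" is marked at week 0, at the column "Post-intervention 13 weeks" and at weeks 13–24. Its cell for the intervention period, weeks 1–12, is blank. The section on follow-up visits instead puts the end-of-treatment assessment in the final week of treatment.

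The monthly contacts described during treatment cover diet, sunlight exposure and physical activity. The safety section adds recording of complaints and adverse events, discontinuation for serious complications, and prompt discussion by a qualified medical practitioner of any abnormality that is found. It names no laboratory test during treatment.

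**The concern.** A stopping criterion that depends on a laboratory value protects a patient only if someone obtains that value while there is still treatment to stop. Here the thresholds and the blood-sampling schedule do not fit each other. The safety section says that there is no special data monitoring committee and that the ethics committee reviews yearly, whereas the intervention lasts 12 weeks. Patient-level stopping is therefore the main safeguard within treatment, and its laboratory part has no planned measurement behind it.

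Two further defects affect the same rule. The calcium limit cannot be applied as printed. The two timings of the end visit also leave open whether a high value at that visit counts as early termination: it could in the last week of treatment, but not at week 13, when treatment has ended.

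**Working it through.** **1. Conditions that need a blood result.** Splitting (c) at its alternative gives four conditions: calcium, 25(OH)D, a planned change to a stronger drug, and HbA1c. Three of the four need a laboratory value.

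**2. Planned blood samples.**

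| Source in the protocol article | Baseline | Weeks 1–12 | End of intervention | Later |
|---|---|---|---|---|
| Outcome measures and measurement procedures | yes | none | yes | 3 months after |
| Table 2, blood row | week 0 | blank | week 13 | weeks 13–24 |
| Follow-up visits | – | none before the last week | last week of treatment | – |

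Scheduled samples between baseline and the end-of-intervention visit: 0. On the earliest timing, the first planned post-baseline result comes when about 11 of the 12 weeks have been given. A value from that draw might formally meet a criterion, but almost no treatment would be left to stop.

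**3. Calcium unit.** 2.65 mmol/L = 2,650,000 nmol/L. If mmol/L is meant, the printed limit is too low by a factor of 10^6, and read literally it would stop every patient.

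**4. Reach of the 25(OH)D limit.** Patients enter "with serum 25(OH)D concentrations < 20 ng/mL on screening". To exceed 100 ng/mL they need a rise of more than 100 − 20 = 80 ng/mL, on 1000 IU/day, which is half the 2000 IU/day upper dose cited in the safety section. This criterion is very unlikely to be met, so in practice the gap concerns calcium and HbA1c.

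**5. Size for HbA1c (illustration only).** The documents give the entry limit (8.0%), the stopping limit (8.5%) and the group size (60/4 = 15). They give no distribution. I assume entry values x uniform on 6.5–8.0%, no mean change, and a normally distributed change with SD s between 0.4 and 0.8 points. Then P(HbA1c > 8.5) is the average over x of 1 − Φ((8.5 − x)/s):

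| s | Proportion above 8.5% | Of 15 control patients |
|---|---|---|
| 0.4 | 0.0135 | 0.20 |
| 0.6 | 0.0453 | 0.68 |
| 0.8 | 0.0853 | 1.28 |

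For a patient entering at the 8.0% limit, 1 − Φ(0.5/0.4) = 0.106 and 1 − Φ(0.5/0.8) = 0.266.

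**6. Calcium rate.** The documents give nothing from which to derive one.

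**The case against.** The best defence is that the schedule is weak evidence of absence. Every assessment row in Table 2 is an outcome group. The table's caption calls it an example template, and it leaves out the monthly questionnaires that the text describes, so it is not exhaustive. A condensed article may omit an interim safety sample that the full protocol contains. The safety section also provides for abnormalities found during the intervention and lets patients see their own practitioner, so the criteria can act on results obtained for clinical reasons. Patients are further protected by the modest dose, by the exclusion of kidney insufficiency and of regular calcium supplements in the past year, and by the drug-change criterion, which needs no study sample.

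Much of this stands. It limits the likely harm, and it means that an interim sample may exist elsewhere. It does not remove the mismatch. The article prints an explicit blank cell, its text gives the same three times, and the safety section plans no test that would detect an abnormality. The unit error and the double timing of the end visit are on the page whatever the full protocol says.

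A reader might go further and infer unequal detection between arms. The exercise arms train under supervision "3 times a week for 3 months", which is 3 × 12 = 36 sessions against none in the other two arms. The documents do not support that inference. Sessions with a trainer are not blood tests, and nothing in the article has the trainer order or prompt one.

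**Conclusion.** The point holds as a minor safety and consistency correction. Three of the four early-termination conditions have no scheduled test in weeks 1–12, the calcium limit carries the wrong unit, and the end visit is timed in two ways.

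The number of patients affected is probably small. 25(OH)D can be set aside in practice. The HbA1c figures of 1.4% to 8.5%, or 0.2 to 1.3 of 15 control patients, rest wholly on the assumed entry distribution, zero mean change and SD range. Because entry requires stable HbA1c, the upper end may be too high, and some of these patients would be stopped through the drug-change condition anyway.

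A reader might also infer bias in the per-protocol analysis. The article does not say that an end-visit value removes anyone from that analysis, and the intention-to-treat analysis is unaffected, so no analysis bias is shown.

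**What to change.** - Correct the calcium limit to > 2.65 mmol/L.
- Add one calcium and HbA1c check at an existing monthly contact, the same in all four arms, and mark it in Table 2. The qualified medical practitioner already mentioned in the safety section can read the results. Leave out a mid-course 25(OH)D measurement, because it could reveal who is taking vitamin D.
- Give the end-of-intervention visit one time, the same in the follow-up section and Table 2, and state that values from that visit do not count as early termination.
- If the full protocol already has an interim sample, show it in Table 2 instead of adding one.

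The cost is one blood draw per patient, at most 60, plus a few words and one table mark. The article does not say whether the monthly contacts are in person; if they are remote, the draw needs a visit. It describes recruitment as ongoing, so the change could apply to patients still to be enrolled. The unit and the visit time cost only wording.

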### Randomization

All patients who give consent for participation and who fulfill the inclusion criteria will be randomized. An investigator who is independent of this study will randomly divide the subjects into four groups according to a computer-generated random allocation table stratified by age and sex. The treatment allocation code will be placed in an opaque envelope labeled with a sequential number. Group allocation was unknown to participants, investigators, and data collectors. The randomization code was broken after the last participant finished the study. The four groups are as follows: the placebo control group (CG), vitamin D supplementation group (VG), endurance exercise group (EG), and vitamin D supplementation combined endurance exercise group (VEG). All patients will be instructed not to change their levels of general physical activity and dietary habits during the intervention period. Their dietary changes will be recorded monthly as well.

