### Statistical analyses

Based on the relative studies on vitamin D intervention with IR [15], the sample size required for each group was estimated to be 12 with a power of 85%, and an effect size of 0.26 was assumed. Therefore, 48 T2DM patients are required. To account for 20% loss-to-follow-up, a total of 60 T2DM patients will be recruited. Power calculations will be performed using G*Power software version 3.1.9.2 [35].

Descriptive statistics will be calculated using mean (standard deviation) for continuous variables and *n* (%) for categorical variables. Differences will be compared using one-way analysis of variance (ANOVA) for continuous variables and chi-squared tests for categorical variables. Repeated measures ANOVA will be used to test the effect of vitamin D and exercise combined intervention on glucose and lipid metabolism, with adjustment for baseline levels of outcomes. A post hoc test with Bonferroni correction will be used to identify significant differences among the mean values when a significant main effect or interaction is identified. Finally, in the event of possible losses or dropouts, a statistical analysis will be performed by protocol and intention to treat. Data will be entered and cleaned using EpiData version 3.0 and managed and analyzed using the Statistical Package for the Social Sciences. Statistical significance will be set at *P* < 0.05.

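### Allocation is stratified by age and sex, but the stated model adjusts only for the baseline outcome, so precision is forgone to the extent that age and sex are prognostic

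*Protocol article*

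**What the plan says.** Under Randomization, an independent investigator "will randomly divide the subjects into four groups" using a "computer-generated random allocation table stratified by age and sex". The section gives no age cut-points, number of strata or block size.

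Under Statistical analyses, the model is fixed in these terms: "Repeated measures ANOVA will be used to test the effect of vitamin D and exercise combined intervention on glucose and lipid metabolism". The one adjustment attached to that model is stated as "with adjustment for baseline levels of outcomes". No other covariate is named there or elsewhere in the article. Bonferroni-corrected post hoc tests follow a significant main effect or a significant interaction.

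The same section puts the need at 12 evaluable patients per group, 48 in all, for 85% power, and records that "an effect size of 0.26 was assumed". Allowing for 20% loss to follow-up brings recruitment to 60. The calculation does not mention stratification or any variance explained by age and sex.

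**The concern.** Allocation that is balanced within age and sex strata gives every arm nearly the same mix of those factors. Differences between strata then largely drop out of the true sampling error of a group contrast. A model without the factors still counts those differences as residual noise. Its standard errors are therefore larger than the real uncertainty, its intervals too wide, and its tests reject less often than the nominal 5% under the null.

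What is at stake is efficiency. The plan expects 12 evaluable patients per arm and corrects its pairwise comparisons by Bonferroni, so precision is scarce. The two variables that could recover some of it are already needed for allocation.

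**Working it through.** **Inputs from the article.** Four groups, effect size 0.26, 48 evaluable and 60 recruited patients, significance level 0.05, stated power 85%.

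**Assumed, because the article does not state them.** Effect size read as Cohen's f; two visits (m = 2); correlation between visits ρ = 0.5; sphericity. R² is the share of residual variance, after the baseline outcome, that age and sex explain. It is varied over a range.

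**Step 1: reproduce the plan's figure.** For the group-by-time interaction, the noncentrality is λ = f² × N × m / (1 − ρ) = 0.0676 × 48 × 2 / 0.5 = 12.98, with 3 and 44 degrees of freedom. Power is 83.6%, close to the stated 85%. The smallest N for 85% is 50, or 52 with equal groups. The inflation 48 / 0.80 = 60 matches exactly. This agreement depends on the assumptions: with two visits, power at N = 48 is 68% at ρ = 0.3 and 97% at ρ = 0.7. A one-way ANOVA with f = 0.26 gives only 27%, so it is not the calculation behind the 48. The reproduction takes no credit for stratification.

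**Step 2: add age and sex.** One error degree of freedom goes to the baseline covariate, leaving 43; power is 83.5%. Adding age and sex uses two more, leaving 41, and changes the noncentrality to λ / (1 − R²). The standard error shrinks by √(1 − R²).

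| R² (assumed) | λ / (1 − R²) | SE ratio | Power without | Power with | Gain (points) |
|---|---|---|---|---|---|
| 0 | 12.98 | 1.000 | 83.5% | 83.3% | −0.2 |
| 0.05 | 13.66 | 0.975 | 83.5% | 85.4% | about 2 |
| 0.10 | 14.42 | 0.949 | 83.5% | 87.4% | about 4 |
| 0.20 | 16.22 | 0.894 | 83.5% | 91.2% | about 8 |

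If all 60 patients are evaluable, the figures are 91.9% without the factors and 91.8%, 94.5% and 96.7% with them at R² = 0, 0.10 and 0.20.

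**Step 3: check that the tests are conservative.** For a single contrast under balanced stratified allocation, the actual type I error is roughly 2 × [1 − Φ(1.96 / √(1 − R²))]. This gives 4.4% at R² = 0.05, 3.9% at 0.10 and 2.8% at 0.20.

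A simulation of the four-group test used 48 patients, four strata of 12, exact balance within strata and 6,000 runs per setting. Its treatment effect was chosen for the simulation, so its power levels differ slightly from Step 2.

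| R² | Type I error, baseline only | Type I error, plus age and sex | Power, baseline only | Power, plus age and sex |
|---|---|---|---|---|
| 0 | 5.6% | 5.5% | 81.4% | 81.2% |
| 0.10 | 3.3% | 4.9% | 81.1% | 84.9% |
| 0.20 | 2.0% | 5.1% | 81.2% | 89.1% |

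The Monte Carlo standard error near 5% is √(0.05 × 0.95 / 6,000) = 0.3 points, so the values at R² = 0 are compatible with 5%. Without the factors, power stays level as R² rises; only the adjusted analysis improves.

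**Step 4: where the gain disappears.** With age and sex effects identical at both visits, a change-score (time-by-group) test gave 69.4% power with and without the factors, because those effects cancel. In the same setting the baseline-adjusted analysis gave 76.9% without and 80.7% with them, because a baseline slope below 1 removes only part of a stable effect.

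**The case against.** **The article may simply be silent.** It does not say that the baseline outcome is the only covariate, and a full covariate list often sits in an analysis plan, which is not shown here. The version table also records that version 1.3 brought in a fuller analysis plan. This limits the weight of the point but does not remove it. The article does address adjustment, names what it adjusts for, and leaves out the two factors its own randomisation uses. A reader might infer that the two sections contradict each other; they do not. The stated model can be run as written, but it is less efficient than it could be.

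**Balance within strata is assumed.** With simple randomisation inside strata, the unadjusted standard errors would not be systematically too large, so the conservatism in Step 3 would go. This stands. Adjustment for prognostic factors could still sharpen the estimate, but the mismatch with the design would matter less.

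**Age and sex effects may cancel.** This holds for a pure change-score interaction test when the effects are the same at both visits. It does not settle the matter here, because the plan also adjusts for baseline and acts on a significant main effect. In a repeated measures ANOVA, the group main effect is tested against between-patient variation, where age and sex differences sit. Effects of age or sex on the change itself do not cancel either.

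**No prognostic strength is documented.** This is correct, and the size of the gain is therefore conditional.

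**Conclusion.** The point holds as a modest, conditional efficiency correction. The stated model omits the factors used to stratify allocation. If allocation is balanced within strata and age and sex predict the outcome beyond its baseline value, tests will be conservative and the power forgone is about 2 to 8 points for R² from 0.05 to 0.20 at 48 evaluable patients. At R² = 0 nothing is forgone. The figures rest on the assumed R², on two visits with ρ = 0.5, and on reading 0.26 as Cohen's f.

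The documents do not support two stronger readings. A reader might infer that the omission leaves the trial short of its planned power. The stated sample size is approximately reproduced with no credit for stratification, so what is missed is a gain on top of the plan. A reader might also infer bias or excess false positives. The group contrast is not biased by the omission, and any error in the significance level is towards too few rejections.

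**What to change.** In Statistical analyses, extend the adjustment in the primary model to cover the baseline value of the outcome and the randomisation stratification factors, age and sex. Age can enter as a continuous covariate or in the categories used for allocation.

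The cost is one phrase and two or three error degrees of freedom. At N = 48, if the factors turn out not to be prognostic, two degrees of freedom cost about 0.2 points of power (83.5% to 83.3%) and three cost about 0.3 points (83.5% to 83.2%). No new data are needed, since both variables must be known to allocate patients.
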